# Effects of different wavelengths of invasive laser acupuncture on chronic non-specific low back pain: a study protocol for a pilot randomized controlled trial

**DOI:** 10.1186/s13063-021-05038-6

**Published:** 2021-02-05

**Keywords:** Chronic non-specific low back pain, Laser acupuncture, Randomized controlled trial, Study protocol

## Abstract

**Background:**

Chronic non-specific low back pain (CLBP) is a common musculoskeletal disorder for which patients seek complementary and alternative medical treatments, including laser acupuncture (LA). Invasive LA (ILA) involves the simultaneous application of invasive acupuncture treatment at acupoints and focused laser irradiation. The efficacy of ILA for CLBP remains controversial owing to the insufficient clinical trial data. We intend to obtain basic data regarding the efficacy and safety of ILA for CLBP by comparing the effects of different wavelengths of ILA on CLBP.

**Methods:**

This will be a prospective, patient-blinded, parallel-arm, single-center (DongShin University Gwangju Korean Medicine Hospital, Republic of Korea), pilot randomized controlled clinical trial. Forty-five participants with CLBP will be randomized in equal numbers into the control, 650-nm ILA (650 ILA), or 830-nm ILA (830 ILA) group. The control group will receive sham ILA for 10 min and real electroacupuncture (EA) for 10 min. The 650 and 830 ILA groups will receive real ILA (i.e., 650 ILA group, 650-nm wavelength; 830 ILA group, 830-nm wavelength) for 10 min and real EA for 10 min once/day, twice a week for 4 weeks, at bilateral Shenshu (BL23), Qihaishu (BL24), Dachangshu (BL25), and Huantiao (GB30). The primary outcome will be an improvement in pain intensity assessed using the visual analog scale. Scores in the Korean version of the Oswestry Disability Index and the European Quality of Life Five Dimension Five Level scale will be recorded as secondary outcome measures. All scores will be recorded at baseline (before intervention), 4 weeks after the first intervention (at the end of the intervention), and 4 weeks after completion of the intervention.

**Discussion:**

The study is expected to provide preliminary evidence regarding the efficacy, safety, and usefulness of ILA for the treatment of CLBP.

**Trial registration:**

This trial was registered with the Clinical Research Information Service (registration No. KCT0004610; http://cris.nih.go.kr). Registered on 7 January 2020.

**Supplementary Information:**

The online version contains supplementary material available at 10.1186/s13063-021-05038-6.

## Background

Chronic non-specific low back pain (CLBP) is one of the most common, expensive, and disabling musculoskeletal conditions. CLBP is defined as pain and soreness, muscle tension, or stiffness in the lumbosacral area of the spine that does not have a specific underlying pathological cause and persists for > 3 months [1–3]. Functional limitations and consequent disability cause a heavy economic burden and poor quality of life in individuals and the society. In the USA alone, the expenditure on low back pain (LBP) has been estimated to be at least $100 billion per year [4]. A previous study reported the burden of chronic back pain in the general population and underscored its correlation with quality of life [5].

A cohort study demonstrated that > 51% of patients with LBP received complementary and alternative medicine (CAM) therapy during their 1-year follow-up [6]. In CAM, acupuncture, herbal medicine, thermal therapy, and spinal manipulative therapy have been used in patients with CLBP [7, 8]. Among CAM therapies, acupuncture is one of the most popular options [9]. On the basis of 5 systematic reviews (1 of high quality, 2 of moderate quality, and 2 of low quality), acupuncture, used either in isolation or as an adjunct to conventional therapy, provides short-term improvements in pain and function in patients with chronic LBP [10].

Low-level laser therapy (LLLT) is a noninvasive light source treatment that emits no heat, sound, or vibrations, but may act on cells via non-thermal or photochemical reactions [11] and can promote wound healing, peripheral nerve regeneration, pain relief, and further reduction of inflammation [12]. Laser acupuncture (LA), which involves focused irradiation at specific points, that is, at the most common traditional acupuncture points, with a low-intensity laser, has been commonly used over the last 35 years [13, 14]. Although LA treatment is a subgroup of LLLT, it is considered to be a separate form of treatment. Instead of using the direct effect of light on tissues to initiate a physiological response, the selection of points is based on a diagnostic and therapeutic paradigm defined by acupuncture theories [13, 15]. Different wavelengths, energy doses, and acupoints affect the effects of laser acupuncture [16–18].

A meta-analysis of randomized controlled trials (RCTs) of LLLT (including LA) for CLBP reported a moderate quality of evidence (GRADE) to support a clinically important benefit of LLLT for CLBP in the short term, which was only seen after higher laser-dose interventions and in participants with a shorter duration of back pain [14]. However, a couple of RCTs reported that noninvasive LA did not show significant effects as compared with sham lasers in patients with LBP [13, 19].

Noninvasive LA is applied to the skin and can be used as an alternative to needles through the use of laser-emitting devices. Invasive LA (ILA) involves the simultaneous application of invasive acupuncture treatment at acupoints and focused laser irradiation using a laser machine connected to an acupuncture needle consisting of an optical fiber-coupled laser diode. Previous studies showed that ILA combined with other treatments has significant effects on neuropathic pain and rheumatoid arthritis in rat models [20, 21]. However, relatively little evidence was obtained from clinical trials regarding the use of ILA for CLBP, especially rigorous randomized controlled clinical trials reporting on the efficacy of ILA. Therefore, we intend to obtain basic data regarding the efficacy and safety of ILA for CLBP by comparing the effects of different wavelengths of ILA.

## Methods/design

### Aims

This study will investigate the efficacy of ILA in the treatment of CLBP by comparing the effects of different wavelengths of ILA (650 and 830 nm) in terms of improvements in pain intensity, functional status, and patient quality of life.

### Hypothesis

The null hypothesis is that different wavelengths of ILA will provide similar improvements in pain intensity, functional status, and quality of life in patients with CLBP.

### Study design and setting

This manuscript was written in accordance with the SPIRIT (Standard Protocol Items: Recommendations for Interventional Trials) and CONSORT (Consolidated Standards Of Reporting Trials) 2010 guidelines [22, 23] (Additional file 1).

This study was a prospective, patient-blinded, parallel-arm, single-center (DongShin University Gwangju Korean Medicine Hospital, Republic of Korea), pilot randomized controlled clinical trial with a 1:1:1 allocation ratio. A total of 45 participants who met the inclusion criteria will be randomly allocated to the control, 650-nm ILA (650 ILA), or 830-nm ILA (830 ILA) group (*n* = 15 in each group). Participants in the control group will receive sham ILA for 10 min and real electroacupuncture (EA) for 10 min, while those in the 650 and 830 ILA groups will receive real ILA (i.e., 650 ILA group, 650-nm wavelength; 830 ILA group, 830-nm wavelength) and real EA both for 10 min. Participants will receive treatment once/day, twice/week for 4 weeks, at bilateral Shenshu (BL23), Qihaishu (BL24), Dachangshu (BL25), and Huantiao (GB30).

The primary outcome will be improvements in pain intensity assessed using the visual analog scale (VAS). The secondary outcome measures will include changes in scores in the Korean version of the Oswestry Disability Index (ODI) and the European Quality of Life Five Dimension Five Level scale (EQ-5D-5L). All scale scores will be recorded at baseline (before intervention), 4 weeks after the first intervention (i.e., at the end of the intervention), and 4 weeks after completion of the intervention.

This study protocol complies with the principles of the Declaration of Helsinki and Korean Good Clinical Practice guidelines and was approved by the Ministry of Food and Drug Safety (Medical Device Clinical Trial Plan approval No. 1039). The trial was registered with the Clinical Research Information Service (registration No. KCT0004610; registration date: January 7, 2020; http://cris.nih.go.kr). The study design is summarized in Figs. 1 and 2.

**Fig. 1 Fig1:**
[figure not shown]
Study design flow chart

**Fig. 2 Fig2:**
[figure not shown]
Standard Protocol Items: Recommendations for Interventional Trials Statement (SPIRIT). The figure shows the enrolment, interventions, and data collection

### Participant recruitment

Participants will be recruited at the DongShin University Gwangju Korean Medicine Hospital, Republic of Korea. The study will be advertised through local newspapers, the Internet, and posters in communities and hospitals. Interested individuals will receive instructions for clinical trial participation through phone calls or visits to our hospital. When interested individuals visit the clinical research center at DongShin University Gwangju Korean Medicine Hospital, they will receive an explanation about the study from the clinical research coordinator (CRC) and will be asked to voluntarily sign an informed consent form prior to participation.

To facilitate participation in the study, the CRC will adjust the treatment and evaluation schedules of each individual participant. Every time the participants visit, the CRC will explain the schedule for the following visit and will remind the participant of the schedule by phone on the day before the appointment. The CRC will continuously monitor the medical condition of the enrolled participants to ensure their adherence to the intervention protocols.

### Inclusion criteria

Participants who meet all of the following criteria will be included in this trial: (1) aged between 19 and 70 years, (2) has CLBP lasting for at least the previous 3 months, (3) scored ≥ 40 points on a 100-mm VAS for pain at the time of screening, (4) has adequate level of Korean language proficiency for the reliable completion of all study assessments, and (5) voluntarily provides informed consent.

### Exclusion criteria

The exclusion criteria are as follows: (1) radicular pain or progressive neurological deficits; (2) diagnosis of a serious spinal pathology (cancer, recent vertebral fracture, spinal infection, or inflammatory spondylitis); (3) presence of a serious chronic disease (cancer, severe cardiovascular, cerebrovascular, liver, kidney disease, or diabetic neuropathy); (4) history of treatment for alcohol/drug dependency or mental illness (schizophrenia, dementia, or epilepsy) in the 6 months preceding enrollment; (5) LBP not caused by a spinal or soft tissue disease (trauma, ankylosing spondylitis, fibromyalgia, rheumatoid arthritis, or gout); (6) presence of contradictions for LA or EA, such as blood clotting abnormalities (hemophilia), severe skin disease in the lumbar region, presence of metallic devices in the lumbar spine, or presence of electronic medical devices (pacemaker); (7) previous lumbar spinal surgery within a year or scheduled procedures during the study; (8) pregnancy or planning to become pregnant; and (9) concurrent participation in other clinical trials.

### Dropout criteria

Participants will be dropped from the trial under the following conditions: (1) < 75% compliance with the protocol procedures (participating in < 6 of the 8 scheduled treatment sessions); (2) occurrence of a serious adverse event (SAE); (3) reluctance to continue the trial; (4) incomplete data that could influence the trial; (5) large errors in protocol or significant deviations in implementation; or (6) if the principal investigator (PI) or institutional review board (IRB) decides to terminate their participation in the trial.

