### Statistical analysis

A statistician not involved in data collection will analyze the final data. We will perform a full analysis set (FA group) to assess the efficacy and a supplementary per-protocol analysis (PP group). We will compare the results of the statistical analyses between the FA and PP groups and confirm any statistically significant differences between the groups. If a significant difference exists between the PP and FA groups, the cause will be reviewed and reflected in the efficacy assessment. Missing values will be obtained using the “last observation carried forward” method. Interim analyses will not be performed. All statistical analyses will be performed using the SPSS version 21 software.

Baseline characteristics will be described and compared between the groups. Continuous data will be presented as means and standard deviations and compared using the independent *t* test or Mann-Whitney *U* test (nonparametric test). Categorical data will be presented as frequencies and percentages and compared using the chi-square or Fisher exact test.

Within each group, changes in VAS, ODI, and EQ-5D-5L scores at 4 weeks (the end of intervention) and 8 weeks (4 weeks after the end of intervention) after the start of intervention, relative to the baseline score, will be analyzed using a paired *t* test or Wilcoxon signed rank test (nonparametric test). Trends over time and time-by-treatment interactions will be explored using repeated-measure analysis of variance. The degrees of changes in the VAS, ODI, and EQ-5D-5L scores at each time point between the groups will be evaluated using the independent *t* test or Mann-Whitney *U* test (nonparametric test). Subanalyses will be performed according to participant age. All reported *p* values will be two-sided, with 95% confidence intervals. A *p* value < 0.05 will be considered statistically significant.

A safety assessment will be performed for all AEs that will occur during the study period. The incidence of AEs and SAEs will be summarized by group and analyzed using the chi-square or Fisher exact test.

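### The dropout criteria remove randomised participants from the trial for events after randomisation, with no stated follow-up, so the full analysis set is not secured for the primary comparison

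*Protocol article*

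**What the plan says.** All references are to the protocol article.

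- **Dropout criteria.** The list opens: "Participants will be dropped from the trial under the following conditions: (1) < 75% compliance with the protocol procedures". Criterion (1) is attendance at fewer than 6 "of the 8 scheduled treatment sessions". Criterion (2) is a serious adverse event (SAE) and (3) is unwillingness to continue. Criterion (4) is "incomplete data that could influence the trial", (5) covers large protocol errors or significant deviations, and (6) is a decision by the principal investigator or the ethics board. One consequence applies to all six: "Participants will be dropped from the trial under the following conditions".
- **Statistical analysis, analysis sets.** "We will perform a full analysis set (FA group) to assess the efficacy and a supplementary per-protocol analysis (PP group"). Missing values are filled by last observation carried forward (LOCF).
- **Statistical analysis, FA against PP.** "If a significant difference exists between the PP and FA groups, the cause will be reviewed and reflected in the efficacy assessment".
- **Outcome measurements.** VAS, ODI and EQ-5D-5L are scored at baseline, at the end of treatment (week 4) and 4 weeks later (week 8). The primary endpoint is the week-4 VAS.
- **Sample size estimation.** A 20% dropout rate is planned, with 15 participants per arm and 45 in total.

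The article does not say whether a dropped participant is still assessed at weeks 4 and 8, or whether that participant stays in FA.

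**The concern.** Criteria (1), (4) and (5) are the usual grounds for leaving someone out of a PP set. Here they, and an SAE under (2), end participation in the trial. Stopping treatment, stopping follow-up and leaving the analysis are three different things, and the rule does not separate them.

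Attendance and willingness to continue can depend on how well a participant is responding. Removal can also depend on allocation. The Discussion says the acupuncturists cannot be blinded, Randomization has the principal investigator or the practitioners open the envelopes, and criteria (4), (5) and (6) involve judgement. If removal differs between arms for reasons linked to response, the comparison is no longer the randomised one.

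Two further problems lie close by. Criterion (4) removes people for incomplete data while the analysis section imputes missing data. And the sentence on FA and PP gives a supplementary analysis an undefined part in the efficacy conclusion once results are known.

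**Working it through.** **1. The plan's own figure.** Taking 12 per arm and 20% dropout: 12 / (1 − 0.20) = 15 per arm, and 3 × 15 = 45. This reproduces the stated size. The point below does not change it.

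**2. When criterion (1) can apply.** 6/8 = 75% and 5/8 = 62.5%, so a third missed session (8 − 3 = 5) meets the criterion. That can happen before week 4, when the only score on file is baseline.

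**3. Two readings of being dropped.**

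*Reading A: dropped participants leave the data.* At the planned rate 15 × 0.80 = 12 per arm remain, so 36 of 45 are analysed and 9 are lost. FA moves towards PP.

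*Reading B: dropped participants stay in FA with LOCF.* Anyone dropped before week 4 has baseline carried forward, so the VAS change is baseline − baseline = 0.

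**4. Size under each reading.** The article gives no SD or effect size. Assumptions: 15 per arm, SD of VAS change 20 mm, control change −15 mm, and dropout either unrelated to response or correlated 0.5 with poor response. The results are simulated mean differences, laser minus control (negative favours laser). In the unequal rows the laser arm has the higher dropout.

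| Dropout, control / laser | Correlation | True difference | Reading A | Reading B |
|---|---|---|---|---|
| 20% / 20% | 0 | 0 | 0.0 | 0.0 |
| 20% / 20% | 0.5 | 0 | −0.1 | 0.0 |
| 20% / 20% | 0 | −10 | −10.0 | −8.0 |
| 20% / 20% | 0.5 | −10 | −10.0 | −8.0 |
| 0% / 20% | 0 | 0 | 0.0 | +3.0 |
| 0% / 20% | 0.5 | 0 | −3.3 | +0.3 |
| 7% / 33% | 0 | 0 | 0.0 | +4.0 |
| 7% / 33% | 0.5 | 0 | −3.9 | +1.7 |

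Hand checks for Reading B with dropout unrelated to response:
- Equal 20% dropout: 0.80 × (−10) = −8.0 mm.
- 0% against 20%: 3/15 × 15 mm = 3.0 mm.
- 1 of 15 against 5 of 15: 4/15 × 15 mm = 4.0 mm.

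The Reading A bias scales with the SD: 3.26/20 = 0.163 SD and 3.86/20 = 0.193 SD. At an SD of 15 mm that is 2.4 to 2.9 mm, and at 25 mm it is 4.1 to 4.8 mm.

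Upper bound for Reading A: if exactly the worst 20% of responders leave one arm and nobody leaves the other, the remaining mean shifts by φ(−0.8416)/0.80 = 0.350 SD. That is 0.350 × 20 = 7.0 mm.

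**5. Criterion (4) beside the LOCF rule.** A missing week-4 VAS is incomplete data on the primary endpoint, so it can meet criterion (4). It is also a missing value, so LOCF applies. The article does not say which rule takes precedence, who decides, or when.

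**6. The FA/PP sentence.** PP is a subset of FA, so the two results share most of their participants and are not independent. The article gives no test or threshold for a significant difference between them, and no rule for how its cause would alter the efficacy assessment.

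**The case against.** The best defence is that the article nowhere says dropped participants leave FA. It names FA for efficacy, calls PP supplementary and imputes missing values. Imputation makes most sense if people who stop early are retained. A condensed article may also leave the definitions of FA and PP to a fuller document. That stands as far as it goes: a reader might infer that the dropout rule defeats FA, but this is true only on Reading A. What remains is the stated consequence, removal from the trial with no provision for follow-up. On Reading B that leaves the primary endpoint resting on baseline values for those dropped before week 4.

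Other stronger readings also go further than the text:

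- *The dropout rule contradicts LOCF throughout.* Only criterion (4) overlaps with it, and that criterion is limited to data that could influence the trial. Dropout for the other reasons is compatible with LOCF.
- *Safety follow-up after an SAE is lost.* The section on adverse events covers events during or after treatment, documents all of them and requires immediate SAE reporting. The safety analysis covers the whole study period. Only the later efficacy scores of these participants are in doubt.
- *The dropout criteria let PP replace FA.* The route to the efficacy assessment is a separate sentence, and it says the cause of a discrepancy is reflected, not that PP takes over. Nor does it specify a two-sample test.
- *The bias is 7 mm.* That is a ceiling from perfect selection in one arm. The planned 20% applies to every arm, and equal or unrelated dropout gives a Reading A bias of about 0.

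Finally, this is a 45-person pilot that says its sample is not sufficient to determine efficacy. That lowers the stakes. It does not remove the need for a sound estimate, since the results are meant to be a basis for further research.

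**Conclusion.** The concern holds in a limited form. The protocol drops randomised participants from the trial for post-randomisation events and does not provide for their follow-up, so the data behind the primary comparison depend on which of two readings is applied.

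On Reading A, a spurious difference of about 3 to 4 mm arises if dropout is both related to response and unequal between arms (assumed SD 20 mm, correlation 0.5). On Reading B, a true 10 mm difference shrinks to about 8 mm with 20% dropout per arm. With unequal dropout and no true effect, Reading B gives a difference of 0.3 to 4.0 mm against the arm with more dropout. The millimetre figures for bias rest on assumed inputs, because the article supplies none. The Reading B shrinkage with equal dropout does not depend on the SD.

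The overlap of criterion (4) with LOCF and the open-ended FA/PP sentence are separate, smaller defects in the stated text. No view is taken on when treatment should stop.

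**What to change.** 1. Leave the reasons for stopping treatment unchanged. State that criteria (1), (4) and (5) serve only to exclude a participant from PP.
2. State that the scheduled week-4 and week-8 VAS, ODI and EQ-5D-5L and the adverse event assessments continue for every randomised participant unless consent is withdrawn.
3. Define FA as all randomised participants, analysed in the arm assigned.
4. Reconcile criterion (4) with the missing-data rule, so that a participant with missing data stays in FA and is handled by that rule.
5. Base the efficacy conclusion on FA alone, report PP beside it as a sensitivity analysis, and delete the FA-versus-PP significance rule.

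The cost is wording, a few assessments already on the schedule, and possibly a smaller estimated effect. Two limits should be stated. Trial status reports that recruitment ended in September 2020 and that procedures were expected to finish by the end of December 2020, so item 2 may no longer be achievable for some participants. The analysis wording can still be settled if the data have not yet been analysed. Participants who still lack a week-4 score remain subject to the weaknesses of LOCF, so the change reduces bias but does not guarantee an unbiased estimate.

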### Ethical considerations

This study (protocol ver. 1.2) was approved by the IRB of DongShin University Gwangju Korean Medicine Hospital, Republic of Korea (approval NO: DSUOH-2019-004; date: April 17, 2020). The purpose and potential risks of this clinical trial will be fully explained to the participants and their families. All participants will be asked to provide written informed consent before participation.

